### Study Participants and Eligibility Criteria

We will recruit patients on the basis of the inclusion criteria of exhibiting acute MCA infarct and an NIHSS score of >8 (based on Diener Law) [40], confirmed using brain magnetic resonance imaging (MRI) studies during hospital admission within 72 hours of symptom onset. The exclusion criteria will be as follows: clinical history of major stroke; significant head injury; brain tumor; major psychiatric illness; progressive neurodegenerative disorder; central nervous system infection; epilepsy that may precipitate seizures; use of AEDs, including LEV or PER; being pregnant or lactating; history of inadequate medical compliance; or any other significant major systemic disease with safety concerns, as determined by a physician.

### Intervention

The participants will be divided into 3 groups: the control (placebo) group and the 2 experimental groups (LEV and PER). The patients, investigator, study assessors, and data analysts will remain blind to the treatment assignments from the time of randomization. Because we will conduct block randomization for group allocation, we anticipate that the percentage of patients receiving tissue plasminogen activator or intravenous thrombectomy will be similar in the 3 groups.

The major MCA infarctions typically require the early implantation of a nasogastric tube, and to account for the design of blinding, preventive drugs will be administered in powdered form. The study team works with pharmacists to ensure that medications for the experimental and control groups have similar color, fragrance, and taste. After being ground up, the drugs are packaged in identical medication bags, and a reminder label is affixed to the outer packaging to remind patients to take their medication regularly and for the appropriate duration.

The three groups are described as follows, and the study flowchart is shown in Figure 1: (1) For the control group, a placebo will be administered to patients, and we will maintain standard stroke care during hospital admission if no acute seizure occurs during this period. If an acute seizure occurs, unblinding will be performed, and we will administer AEDs not including LEV or PER; the patient will be maintained on these AEDs. (2) For the LEV group, we will prophylactically administer 1000 mg of LEV per day to patients from the first day of admission in addition to standard stroke treatment. The LEV treatment duration will be 3 months. (3) For the PER group, we will prophylactically administer 4 mg of PER per day to patients from the first day of admission in addition to standard stroke treatment. The PER treatment duration will be 3 months. (4) After the patient is discharged from the hospital, their respective medication will be administered orally for up to 3 months. (5) All patients will receive follow-up for 18 months, and the incidence of late-onset epilepsy will be documented. Seizure characteristics, including semiology, frequency, and severity, will be analyzed in the 3 groups. The relationship of seizure semiology to stroke-related localization will be verified. (6) For those who have acute seizures during hospital admission, unblinding will be performed, and either LEV or PER will be administered for treatment according to their group. The dosage will be adjusted according to real clinical needs. These patients will be treated as having epilepsy based on the 2016 definition of epilepsy [41] and be maintained on LEV or PER after hospital admission. The administration of LEV or PER to patients with acute seizures will still be considered prophylactic therapy because patients with acute seizures have a considerably higher risk of developing poststroke epilepsy. (7) Because up to 20% of patients with anterior circulation ischemic stroke may experience electrographic seizures during the acute stage of stroke without clinically overt seizures [42], we will arrange 1 routine electroencephalogram (EEG) at the acute stage for each patient. Prophylactic AED therapy will be administered according to the group the patient is allocated to if any electrographic seizure, including periodic lateralized epileptiform discharge (PLED), is identified in the EEG. (8) Unblinding will be implemented at 3 months, and the final analysis will be conducted at 18 months.

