## Introduction

### Background

Advances in stroke treatment have caused a considerable reduction in stroke mortality; however, the number of stroke survivors living with disability has increased significantly. Seizures and epilepsy related to ischemic stroke are common, and poststroke epilepsy is a significant clinical problem for stroke survivors. Stroke is the most common cause of epilepsy in older adults and for patients older than 65 years of age, and poststroke epilepsy accounts for 30%-50% of new-onset seizures [1]. The incidence of early seizures (occurring within the first 1-2 weeks of stroke) is 2.4%-5.4%, and the risk of poststroke late seizures (seizures occurring later than after 14 days of stroke) is approximately 7%-18% [1,2]. Late-onset poststroke epilepsy has a higher recurrence rate of up to 71.5% within 10 years after stroke [3]. Our previous study demonstrated that seizures during stroke increase overall morbidity and mortality [4]. The stroke severity, location (for example, middle cerebral artery [MCA] infarcts in our study), and the type of pathological changes, genetic factors, and pre- and postinjury exposure to nongenetic factors influence the susceptibility of patients with ischemic stroke [5,6]. The standardized morbidity rate of developing epilepsy is highest during the first year after stroke. In addition, higher National Institutes of Health Stroke Scale (NIHSS) score [7], cortical involvement, younger age, and central nervous system morbidities are associated with higher risk of poststroke epilepsy [1,8].

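### The protocol does not give one arm-neutral definition of the primary event for patients with an acute in-hospital seizure; read literally, the event could differ by arm and mix acute with late seizures

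*Protocol article*

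**What the plan says.** All of this is in the protocol article.

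- **Intervention, item (6)** deals with acute seizures during admission: "unblinding will be performed, and either LEV or PER will be administered for treatment according to their group". It continues: "These patients will be treated as having epilepsy based on the 2016 definition of epilepsy". It then adds "The administration of LEV or PER to patients with acute seizures will still be considered prophylactic therapy", and gives as the reason "because patients with acute seizures have a considerably higher risk of developing poststroke epilepsy".
- **Intervention, item (1)** covers the same event on placebo: "If an acute seizure occurs, unblinding will be performed, and we will administer AEDs not including LEV or PER". Those patients stay on the other AEDs. The item does not say whether they are regarded as having epilepsy.
- **Intervention, item (5)** applies to everyone: "All patients will receive follow-up for 18 months, and the incidence of late-onset epilepsy will be documented".
- **Outcome Measures, Primary Outcome** names the incidence of poststroke epilepsy, with seizure severity, at the end of the study. It sets no boundary between early and late seizures. It specifies intention-to-treat analysis and individual unblinding if a seizure occurs during the drug period.
- **Background** separates early seizures (first 1-2 weeks, 2.4%-5.4%) from late ones (after 14 days, about 7%-18%).
- **Procedure and Assessment** says that the baseline EEG before AEDs serves to exclude patients with early or concurrent seizures.

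**The concern.** Item (6) can describe only the two active arms, because placebo patients with an acute seizure receive neither study drug. It is also the only place that says when a patient is regarded as having epilepsy, and epilepsy is the primary outcome. The placebo item has no counterpart. Item (6) is also at odds with itself: the same patients have epilepsy in one sentence and are at risk of developing it in the next.

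Two things are at stake.

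- If the label were carried into the outcome, the same seizure would be an event on LEV or PER and not on placebo, which works against the drugs. Because unblinding comes first in item (6), the label could be assigned with the arm known.
- If acute seizures counted in every arm, part of the primary outcome would measure suppression of acute seizures by an antiseizure drug. The trial asks whether early treatment prevents later epilepsy.

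**Working it through.** **Step 1: the passages side by side.**

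| Question | LEV/PER | Placebo |
|---|---|---|
| Acute in-hospital seizure: unblinded? | Yes, item (6) | Yes, item (1) |
| Continuing AED? | Yes, study drug | Yes, other AEDs |
| Called epilepsy? | Yes, item (6) | Not stated |
| Event documented over 18 months | Late-onset epilepsy, item (5) | Late-onset epilepsy, item (5) |
| Early/late boundary in the primary outcome | None | None |

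The windows do not match either. Item (6) is tied to the hospital stay, whereas Background divides early from late at 14 days. A seizure in hospital after day 14 would be acute under one and late under the other.

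**Step 2: size, as an illustration.** The protocol gives no figure for this, so there is none to reproduce. Inputs:

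- early risk e = 2.4% to 5.4% and late risk l = 7% to 18% (Background);
- 180 patients (Methods, Overview) in three equal groups (Randomization and Blinding), so 60 per arm and 120 on active drug.

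Assumptions: no drug effect, the same acute risk in each arm, and acute and late seizures independent.

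- Patients with either kind of seizure: e + l − e·l.
- Gap if acute seizures count on active drug only: (e + l − e·l) − l = e(1 − l).
- Risk ratio in that case: (e + l − e·l)/l.
- Share of patients with an event who had an acute seizure, if counted in all arms: e/(e + l − e·l).

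| e | l | Either | Gap (points) | Risk ratio | Share |
|---|---|---|---|---|---|
| 2.4% | 7% | 9.23% | 2.23 | 1.32 | 26% |
| 2.4% | 18% | 19.97% | 1.97 | 1.11 | 12% |
| 5.4% | 7% | 12.02% | 5.02 | 1.72 | 45% |
| 5.4% | 18% | 22.43% | 4.43 | 1.25 | 24% |

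Active-arm patients affected: 120 × 2.4% = 2.9 to 120 × 5.4% = 6.5, about 3 to 6.

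**Step 3: overlap.** Item (6) itself says that acute seizures raise the later risk, so independence is generous to the concern. At e = 5.4% and l = 7%, suppose half of the patients with an acute seizure also have a late one (an assumption). The active-arm figure is then 7 + 5.4 × 0.5 = 9.7%, the gap 2.7 points and the risk ratio 9.7/7 = 1.39. Patients counted only because of an acute seizure fall from 5.02/12.02 = 42% to 2.7/9.7 = 28% of those with an event. The share with any acute seizure rises to 5.4/9.7 = 56%, because the denominator shrinks.

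**Step 4: effect on a real benefit.** Suppose the drugs halve late seizures and leave acute ones unchanged (an assumption), so the late-only risk ratio is 0.50.

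- e = 2.4%, l = 18%: active 2.4 + 9 − 0.216 = 11.18%. Risk ratio 11.18/19.97 = 0.56 if acute seizures count in all arms, 11.18/18 = 0.62 if on active drug only.
- e = 5.4%, l = 7%: active 5.4 + 3.5 − 0.189 = 8.71%. Risk ratio 8.71/12.02 = 0.72 if in all arms, 8.71/7 = 1.24 if on active drug only.

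**The case against.** A reader might infer that the protocol does count acute seizures as primary events, and only under LEV and PER. The text does not support that. The classification sentence stands in the Intervention section, between dose adjustment and continuation of the drug, and can be read as a reason for continuing treatment. The Primary Outcome section neither repeats nor cites it. Item (5) speaks of late-onset epilepsy for all patients. Placebo patients with an acute seizure also stay on AEDs, so the difference in classification is only that item (1) is silent, which is thin evidence in a condensed article. All of this stands, and it is why the point is an unsettled event and not a proven arm-specific endpoint.

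A second objection is that the baseline EEG excludes early seizures. It may remove some, which lowers the figures. It cannot remove seizures later in the admission, and items (1) and (6) exist because such seizures are expected after allocation.

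A third is that an analysis plan may settle the matter. It may, but the conflict is between statements printed in this document. The label uses the outcome's own term with a diagnostic definition attached, and nothing here says that these patients are not counted.

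**Conclusion.** The point holds as a defect of definition. Items (1), (5) and (6), Background, Procedure and Assessment, and the Primary Outcome section do not together say whether an acute in-hospital seizure is a primary event. Followed literally, they allow a count that differs by arm, to the drugs' disadvantage, and that mixes acute with late seizures.

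The size is illustrative. Active-only counting gives a spurious gap of about 2 to 5 percentage points (risk ratio about 1.11 to 1.72), from about 3 to 6 of 120 patients. Counting in all arms makes patients with an acute seizure about 12% to 45% of those with an event.

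These ranges rest on the Background rates, no drug effect, equal acute risk and independence. Given those rates, the gap and the risk ratio are upper bounds if the baseline EEG removes some early seizures or if acute and late seizures are positively associated. The 12% to 45% share is an upper bound only in the first case. Under positive association it is the proportion counted solely because of an acute seizure that falls. The Background rates are not specific to MCA infarction with an NIHSS score above 8, so the trial's own rates may differ.

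This must be fixed, because it concerns what the primary outcome counts in a trial with about 60 patients per arm.

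**What to change.** - State one primary event for all three arms with an explicit time window, irrespective of arm or AED use. One option is the first unprovoked seizure more than 14 days after stroke. That uses the early/late boundary that Background describes, which the trial has not so far adopted as its own.
- Report earlier seizures as a separate outcome and keep those patients in the intention-to-treat set.
- State that the epilepsy label in item (6) is not an outcome rule.
- Add two supportive analyses: any seizure from randomization, and seizures after the 12-week drug period only. The second is needed because a start at day 14 still includes about 12 − 2 = 10 weeks on drug.

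Items (1) and (6) also set different care after an acute seizure. The clinical team must reconcile them; no change of care is proposed here.

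Cost: slightly fewer counted events. No new data are needed, since the time from stroke onset to seizure is already recorded. It does require a documented amendment in a trial that has recruited since August 2020 and unblinds at 3 months, so the record should show that the definition was fixed without reference to outcomes by arm.

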## Methods

### Overview

We will conduct a prospective randomized, triple-blind, and placebo-controlled study. To calculate the appropriate sample size, we took into account various factors including the population size, margin of error, confidence level, expected variance, number of patients with MCA infarcts admitted to our medical center annually, and potential loss rate. We used G*Power software (Heinrich-Heine-Universität Düsseldorf) to perform these calculations. Specifically, we used an effect size ranging from 0.25 to 0.4, α error probability of .05, power of 0.5, 3 groups, 2 measurements, and a correlation of 0.05 between repeated measures. The resulting total sample size ranged from 51 to 120. Based on the potential number of patients admitted to our medical center and the expected loss rate, we estimated that enrolling 180 cases would be reasonable.

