### Outcome Measures

#### Primary Outcome

The primary outcome measure will be the incidence of poststroke epilepsy and seizure severity at the end of the study period. Univariate ANOVA of the LEV, PER, and placebo groups will be performed. Intention-to-treat analysis will be performed. Participants will be followed up 1, 3, 6, 9, 12, and 18 months after stroke. If a seizure occurs during the prophylactic medication administration period, individual unblinding and adjustment of AEDs will be implemented. If a seizure occurs after the prophylactic medication administration period, ordinary medical care will be provided. We will record seizure type and duration after stroke onset at seizure occurrence **(**Table 1 and Figure 2).

**Table 1 table1:** Summary of follow-up visits.

Visiting time	Within 3 days	3 months	6/9/12 months	18 months
NIHSS^a^	✓			
mRs^b^	✓			✓
MRI^c^	✓			
EEG^d^	✓			
Start of medication	✓			
TEAE^e^	✓	✓		
Occurrence of seizure	✓	✓	✓	✓
Occurrence of death	✓	✓	✓	✓

^a^NIHSS: National Institute of Health Stroke Scale.

^b^mRs: modified Rankin scale.

^c^MRI: magnetic resonance imaging.

^d^EEG: electroencephalograph.

^e^TEAE: treatment-emergent adverse event.

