According to the existing literature, late-onset seizures following a stroke typically exhibit a peak incidence between 6 and 12 months after the initial event [1]. Studies have shown that after an ischemic stroke, the highest risk for the occurrence of the first unprovoked poststroke seizure is observed during the initial follow-up year [5,49]. Furthermore, another study has reported the annual event risk of seizures after the first-ever ischemic stroke, indicating a risk of 6.3% after 1 year, 2.4% after 2 years, 1.3% after 3 years, and 0.3% thereafter [50]. Although the annual risk of seizures may indeed increase in subsequent years, given the highest risk observed during the first year and considering the practical feasibility of our protocol, we have chosen an 18-month follow-up period at this stage.

In terms of stroke severity, minor strokes (those with a small lesion size) are less likely to lead to the development of poststroke epilepsy. For each patient, we routinely arrange for MRI scans as a standard imaging procedure to assess the stroke, including its size, location, and the presence or absence of hemorrhagic transformation during admission. We do not typically perform brain computed tomography (CT) scans. It is worth noting that the absence of hemorrhagic transformation at the onset of the stroke does not eliminate the possibility of it occurring later during the acute stage. In the event of acute deterioration in neurological symptoms and signs, we arrange for follow-up brain MRI or CT scans and provide standard care.

In our protocol, we initiate treatment for patients with PLEDs. PLEDs have been considered to have a high association with seizures [51,52], and among the epileptiform abnormalities, the presence of lateralized periodic discharges was associated with a significantly increased risk of seizure [53]. In addition, PLEDs were associated with an acute process and occurred early during the course of the illness, with stroke being the main etiology [52].

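### Unblinding is scheduled at 3 months, for no named role, although the primary outcome is collected to 18 months in a trial described as triple-blind

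*Protocol article*

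**What the plan says.** The Overview of the Methods describes the design: "We will conduct a prospective randomized, triple-blind, and placebo-controlled study". The Intervention section says who is blind: "The patients, investigator, study assessors, and data analysts will remain blind to the treatment assignments from the time of randomization". The section on randomization and blinding adds clinicians and data collectors. Neither section says when blinding ends.

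The last item of the numbered list under Intervention then sets a date: "Unblinding will be implemented at 3 months, and the final analysis will be conducted at 18 months". Month 3 is also when study drug stops. The item names no role and sets no limit.

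Unblinding of a single patient after a seizure is a separate rule. It appears under Intervention for seizures during admission, and under Primary Outcome for seizures while on study drug, where "individual unblinding and adjustment of AEDs will be implemented".

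On the outcome, the Primary Outcome section says: "The primary outcome measure will be the incidence of poststroke epilepsy and seizure severity at the end of the study period". On timing, it says: "Participants will be followed up 1, 3, 6, 9, 12, and 18 months after stroke". The modified Rankin scale is a secondary outcome at 3 and 18 months.

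**The concern.** Three of the judgements behind the primary outcome are clinical: whether an episode was a seizure, whether the patient now has epilepsy, and how severe the seizures are. They rest largely on what the patient or family reports and on the clinician's reading of it. Table 1 schedules an EEG only within the first 3 days, so no planned test anchors events that occur later. The abstract and the Conclusions both state that the team expects fewer and milder events on active drug.

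If the arm is known from month 3, that knowledge can affect what patients report, how an episode is classified, how severity is graded and when later antiseizure treatment begins. The resulting bias falls directly on the comparison that the trial exists to make, and no analysis at 18 months can remove it. The modified Rankin score at 18 months is exposed in the same way.

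**Working it through.** The article gives no figure for how much follow-up, or how many events, would be observed under blind, so there is no stated figure to reproduce. The shares below use its own inputs.

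**Inputs**
- Scheduled unblinding at 3 months; follow-up to 18 months (Intervention).
- Visits at 1, 3, 6, 9, 12 and 18 months (Primary Outcome).
- Annual seizure risk after a first ischemic stroke: 6.3% in year 1 and 2.4% in year 2 (Principal Findings).
- Early seizures 2.4% to 5.4%; late seizures, after day 14, 7% to 18% (Background).
- Assumption, not in the article: risk is spread evenly within each year.

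**Follow-up after unblinding**
- Time: (18 − 3)/18 = 15/18 = 83%.
- Visits: 6, 9, 12 and 18 months, so 4 of 6.

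**Share of late-onset events after unblinding**
- Share = 1 − (risk to month 3)/(risk to month 18).
- Risk to month 18: 6.3% + 2.4%/2 = 7.5%.
- Risk to month 3: 6.3% × 3/12 = 1.575%, about 1.6%.
- Share: 1 − 1.575/7.5 = 79%.
- If late seizures are counted only from day 14, with 3 months as 91 days: 6.3% × (91 − 14)/(365 − 14) = 1.38%, and 1 − 1.38/7.5 = 82%.

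The even spread is probably conservative, because the article says that "late-onset seizures following a stroke typically exhibit a peak incidence between 6 and 12 months after the initial event". A peak there moves events from before month 3 to after it.

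**Sensitivity: every early seizure also counts as a primary event**
- Share = late risk × 0.79/(early risk + late risk), where 0.79 is the late share above.
- Lowest: early 5.4%, late 7%: 7 × 0.79/12.4 = 45%.
- Highest: early 2.4%, late 18%: 18 × 0.79/20.4 = 70%.

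**Which reading of the primary outcome the text supports**
- For late-onset events only: the follow-up item under Intervention says "All patients will receive follow-up for 18 months, and the incidence of late-onset epilepsy will be documented". Procedure and Assessment also plans a baseline EEG to exclude patients with early or concurrent seizures.
- For counting early events: another item under Intervention treats patients with acute seizures during admission as having epilepsy.

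The text leans to late-onset events, but both ranges should be shown.

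**The case against.** **The item names no role.** It could mean that patients or treating clinicians learn the allocation when study drug ends, while assessors and analysts stay blind. The text allows this. General unblinding is the more natural reading, since the sentence is unqualified and single-patient unblinding is dealt with elsewhere. Still, a reader who infers that the article expressly unblinds everyone goes further than its words. What stands on either reading is that the passages must be reconciled, because nothing in the article describes blinded assessment after month 3.

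**Most primary events need not fall after unblinding.** This is fair if early seizures count, since the lower end of the range is then 45%.

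**The outcome could turn on two or three reclassified events.** A reader might infer this from the small expected number of events. Assume 60 patients per arm, no losses and risk halved on drug (the halving is an assumption). The 7% to 18% placebo risk then gives 60 × 0.07 + 120 × 0.035 = 8.4 to 60 × 0.18 + 120 × 0.09 = 21.6 events. In a three-group chi-square test:
- Low end: 4/2/2 events (placebo and the two active arms) give p = 0.59. Three more placebo events, 7/2/2, give p = 0.089.
- High end: 11/5/5 give p = 0.14. Two more placebo events, 13/5/5, give p = 0.041.

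So the inference holds at the top of the range and not at the bottom, and it should not be stated generally.

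**Points not to press.** The modified Rankin scale is not scheduled at 6, 9 or 12 months, so only its 18-month reading clearly follows unblinding. Whether the seizure form is completed before a single-patient code break is a detail that a journal article may leave to the full protocol.

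**The article is condensed.** That does not answer this point: the 3-month unblinding is an explicit rule in the text, not an omitted detail.

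**Conclusion.** The concern holds as an internal conflict with a real consequence for the primary outcome. The article schedules an unblinding that it does not restrict, 15 months before the outcome is complete, while describing a triple-blind trial with blind assessors and analysts.

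The conflict itself is certain. Its extent depends on two things the article leaves open: who is unblinded, and whether acute seizures count as primary events. If the unblinding is general, 83% of follow-up time is open-label, together with about 79% to 82% of late-onset events, or about 45% to 70% of events if all early seizures count. The event shares rest on the article's cited risks and on even spread within each year.

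It would be too strong to say that the article shows all roles to be unblinded, or that most primary events are open-label under every definition. The problem needs correction because the outcome is judgement-based and the bias cannot be repaired at analysis.

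**What to change.** Delete the scheduled 3-month unblinding and state that the pharmacist holds the code until the 18-month data are locked. If some unblinding at 3 months is to remain, state exactly who is unblinded. In that case, the people who classify seizures, epilepsy, severity and the modified Rankin score, and the analysts, should stay blind to 18 months; blinded adjudication of events would achieve this. Leave the event-driven unblinding of single patients as it is.

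For patients already unblinded, do not describe the trial as triple-blind after month 3, and report this as a limitation. A split of the primary result by blind status at the event is not a substitute, because patients without an event have no such status.

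The change is an amendment to the text. Study drug has ended by month 3, so it needs no further drug supply and no added visits, and the planned enrolment of 180 is unaffected. The costs are that patients and clinicians learn the allocation later and that, with recruitment open since August 2020, allocations already disclosed cannot be re-blinded. The benefit therefore shrinks with each further patient who passes month 3.
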